# The efficacy and safety of MARS-PD: Meridian activation remedy system for Parkinson’s disease—A single-center, assessor and statistician-blinded, parallel-group randomized, controlled trial protocol

**DOI:** 10.1371/journal.pone.0303156

**Published:** 2024-05-06

## Abstract

**Background:**

Parkinson’s disease (PD) patients face a substantial unmet need for disease-modifying interventions. Potential approaches such as exercise and acupuncture have been investigated to slow PD progression. To address this unmet need, we developed a novel therapeutic approach that integrates acupuncture and exercise: the Meridian Activation Remedy System for PD patients (MARS-PD). Building upon promising outcomes observed in our preliminary pilot study, where MARS-PD exhibited a large clinically important difference on the Movement Disorder Society Unified Parkinson’s Disease Rating Scale Part III (MDS-UPDRS Part III), we embark on a randomized controlled trial with the primary objective of examining the efficacy, safety, and economic impact of MARS-PD.

**Methods:**

In this single-center, assessor and statistician-blinded, parallel-group randomized controlled trial, we aim to investigate the clinical efficacy of MARS-PD through 16 interventions administered over 8 weeks in 88 PD patients. Participants will be randomly assigned to the experimental (n = 44) or control (n = 44) groups. The experimental group will receive MARS-PD intervention alongside standard care, while the control group will solely receive standard care. The intervention period spans 8 weeks, followed by a 12-week post-intervention follow-up. The primary endpoint is the change in MDS-UPDRS Part III score from baseline to the conclusion of the 8-week intervention. Secondary outcomes encompass various assessments, including MDS-UPDRS, International Physical Activity Questionnaire Short Form, Parkinson Self Questionnaire, Parkinson’s Disease Sleep Scale, Timed Up and Go test, GAITRite metrics, Functional Near-Infrared Spectroscopy measurements, smart band outcomes, gut microbiome analysis results, and iris connective tissue texture.

**Discussion:**

Previous studies by the authors have indicated MARS-PD’s safety and benefits for PD patients. Building upon this foundation, our current study aims to provide a more comprehensive and detailed confirmation of the efficacy of MARS-PD.

**Trial registration:**

cris.nih.go.kr KCT0006646 –First posted on 7 October 2021; ClinicalTrials.gov NCT05621772 –First posted on 11 November 2022.

## Introduction

### Background and rationale

Parkinson’s disease (PD), the second most prevalent neurodegenerative disorder, impacts approximately 2–3% of individuals aged 65 and older, manifesting with motor symptoms such as bradykinesia, rigidity, tremor, and postural instability [1]. However, PD is considered to exhibit the fastest growth rate among various degenerative brain diseases [2]. Furthermore, non-motor symptoms such as autonomic dysfunction, constipation, sleep disorders (including rapid eye movement (REM) sleep behavior disorder), and fatigue often precede motor symptoms, broadening the scope of individuals affected by PD when considering prodromal PD patients [3,4].

For many years before it manifests clinically, PD progresses gradually, causing damage to the patients’ multiple nervous systems, including the central, peripheral, and enteric nervous systems [5]. Moreover, people with PD experience a decline in both movement speed and muscle strength, resulting from an altered pattern of motor unit activation. Over the last fifty years, research has revealed a wide range of motor abnormalities and myofiber changes in PD patients, including hypertrophy of slow-twitch Type I myofibers and atrophy of fast-twitch Type II myofibers in various muscles [6]. Several studies have found that type I myofiber grouping in muscles, not just dopaminergic cell damage in the substantia nigra, can influence motor symptoms of PD [7–9], implying that treatments other than dopaminergic drugs, such as exercise, may also be beneficial [10].

Individuals with PD currently face unmet needs in terms of long-term management and treatment strategies, given the absence of specific disease-modifying medications or sustainable interventions available at the moment [11]. Despite a growing body of evidence supporting the disease-modifying impact of various exercise modalities on PD [12], there remains a notable lack of a structured system facilitating consistent and continuous physical activity for symptom management [13]. Meanwhile, studies have indicated that long-term acupuncture, when combined with antiparkinsonian medication, can effectively manage PD. Mizushima et al. demonstrated that acupuncture in conjunction with drug treatment over a five-year period resulted in suppressed disease progression, improved daily life functioning, and enhanced exercise capabilities compared to drug treatment alone [14]. In a network meta-analysis by Kwon et al., various acupuncture treatments, when used alongside conventional levodopa therapy for individuals with PD, exhibited superior outcomes compared to sham acupuncture or exclusive reliance on conventional levodopa therapy [15].

### Objectives

In order to address the need for an effective and sustainable intervention allowing PD patients to maintain their physical activity level over time, we devised the Meridian Activation Remedy System (MARS), integrating acupuncture and exercise. MARS was specifically designed to facilitate the delivery of optimal acupuncture and exercise treatment in hectic clinical environments. Within this framework, patients engage in 20-minute exercise concurrently with the administration of intradermal acupuncture. This integrated approach is strategically designed to amplify efficiency and effectiveness, thereby optimizing therapeutic interventions for patients within busy medical settings.

MARS involves a series of linear movements designed to evenly stimulate the body’s meridians, offering a straightforward and effective routine for PD patients in outpatient settings. The intervention, incorporating both slow (30 beats per minute (BPM)) and fast (120 BPM) movements, aims to activate both slow- and fast-twitch muscle fibers of the patients. In addition, intradermal acupuncture and motions altering the center of gravity were utilized to improve balance and proprioception of the patients [16]. We have observed the effectiveness of MARS for PD in preliminary case study [17] and observational study [18]. In the pilot observational study, MARS (16 interventions administered over 8 weeks) demonstrated a large clinically important difference on the Movement Disorder Society Unified Parkinson’s Disease Rating Scale Part III (MDS-UPDRS Part III) in PD patients (from 20.00 ± 11.78 to 8.85 ± 5.54, p = 0.003). The subsequent phase involves the initiation of a randomized clinical trial to systematically validate the efficacy of MARS. In this single-center, assessor and statistician-blinded, parallel-group randomized controlled trial, our principal aim is to thoroughly assess the efficacy of MARS for PD through a comparative analysis. This entails evaluating a group of PD patients undergoing conventional therapy in conjunction with MARS, juxtaposed with a group solely receiving conventional therapy. Additionally, we will perform safety and economic evaluation of MARS intervention.

## Materials and methods

### Study design and setting

We aim to assess both the clinical efficacy and cost-effectiveness of the Meridian Activation Remedy System for Parkinson’s Disease (MARS-PD). A single-center, assessor and statistician-blinded, parallel-group randomized controlled trial will be conducted at Daejeon Korean Medicine Hospital of Daejeon University, Daejeon, South Korea between 8^th^ April 2022 and December 2024 (i.e., the recruitment period for this study). The study will encompass 88 patients diagnosed with PD, randomly assigned to either the experimental group (undergoing MARS-PD treatment) or the control group (receiving usual care without additional intervention) in a 1:1 ratio. The experimental group will undergo the MARS-PD intervention twice a week for a duration of 8 weeks, followed by a comprehensive assessment during a 12-week follow-up visit. Conversely, the control group will not receive any additional intervention and will adhere to with their usual care for 8 weeks before participating in a follow-up assessment over the subsequent 12 weeks. This trial design is structured to elucidate the potential benefits of MARS-PD, both in terms of clinical outcomes and cost-effectiveness, providing valuable insights into its impact on PD management, utilizing an equivalence framework (assuming, as our null hypothesis, that the MARS-PD therapy and standard care are equivalent). Additionally, participants in the control group, although not receiving the MARS-PD intervention during the study period, will be eligible for compensation treatment upon successful completion of the trial. This compensation involves acupuncture or MARS-PD intervention sessions (based on the subject’s preference) twice a week, totaling one month. We anticipate that offering this compensatory treatment option may further motivate participants to adhere to the study protocols.

The protocol for this clinical trial adheres to the Standard Protocol Recommendations for Interventional Trials (SPIRIT) guidelines (S1 Appendix) [19]. The clinical trial registry number for the current manuscript can be found in CRIS (Clinical Research Information Service, cris.nih.go.kr, no.: KCT0006646) and in ClinicalTrials.gov’s Protocol Registration and Results (PRS) system (no.: NCT05621772). The SPIRIT schedule of enrollment, interventions, and assessments is shown in Fig 1. The flowchart of this study is shown in Fig 2.

**Fig 1 pone.0303156.g001:**
[figure not shown]
The SPIRIT schedule of enrollment, interventions, and assessments.

**Fig 2 pone.0303156.g002:**
[figure not shown]
The flowchart of the study.

### Eligibility criteria

Doctors of Korean Medicine at Daejeon Korean Medicine Hospital of Daejeon University will screen patients for eligibility. The inclusion and exclusion criteria are shown in Table 1. All participants must manually sign a written informed consent from (ICF) prior to any study procedures. During the initial visit, the doctor of Korean medicine will evaluate the Korean Mini-Mental State Examination (MMSE-K) and the Hoehn and Yahr (HY) scale. The test staff will gather vital signs, demographic information, medical and treatment history, laboratory test results, electrocardiogram readings, and chest X-ray results. Eligibility of the subjects will be ascertained through a thorough review of their history, conducted tests, and comprehensive examinations.

**Table 1 pone.0303156.t001:** Inclusion and exclusion criteria.

**Inclusion Criteria:** 45 to 75 years of age Patients with PD, diagnosed according to the United Kingdom Parkinson’s Diseases Society Brain Bank Criteria Hoehn and Yahr scale stage I to III Patients who have voluntarily decided to participate in the clinical study and signed the informed consent form **Exclusion Criteria:** Clinically unstable patients (e.g., elevated aspartate transaminase (AST) or alanine aminotransferase (ALT) more than three-fold the upper limit of normal in the research institute’s laboratory, heart failure, respiratory failure, etc.) Patients who are planning to undergo deep brain stimulation within the study period Pregnant or lactating women Patients with MMSE-K (Mini-Mental State Exam) score of 18 or less If there has been a change in the dosage of antiparkinsonian drugs (e.g., L-dopa, COMT (catechol-O-methyltransferase) inhibitor, Dopamine agonist, MAO-B (monoamine oxidase B) inhibitor, etc.) according to a doctor’s prescription within the last 4 weeks prior to enrollment Patients who are receiving manual therapy, exercise therapy, or rehabilitation therapy for Parkinson’s disease according to a doctor’s prescription within the last 4 weeks prior to enrollment, or are planning to receive such therapy within the study period Patients who are not suitable for participation in this clinical study according to the judgment of the researcher

### Interventions

At a 1:1 ratio, patients will be assigned to either the experimental (MARS-PD intervention) or control (usual care with no additional intervention) groups. Those in the experimental group will undergo the MARS-PD intervention twice a week for 8 a span of weeks, totaling 16 visits. The intervention will be administered by Doctors of Korean Medicine with a minimum of one year of clinical experience in the relevant field, as detailed in the authors’ previous work [16]. In contrast, patients in the control group will adhere to their usual care without any supplementary interventions. Given that the number of steps per day constitutes one of our secondary outcomes, all willing participants, regardless of their group assignment, will receive Samsung Galaxy Fit2 smart band (Samsung Electronics Co., Ltd., Suwon, South Korea), and application-based lifestyle guidance.

During the test period, participants are allowed to engage in personal exercise. However, doctor-prescribed manual therapy, exercise therapy, and rehabilitation treatment specifically tailored for PD are not permitted. This restriction aims to maintain consistency in the intervention conditions and isolate the effects of the MARS-PD being evaluated in the trial.

### Standards for concomitant drug

The utilization of antiparkinsonian drugs, such as levodopa (L-dopa), Catechol-O-methyltransferase (COMT)) inhibitor, Dopamine agonist, Monoamine oxidase B (MAO-B) inhibitor, etc., will be permitted if the dosage has remained stable for more than 4 weeks preceding the initiation of participation in the clinical trial. The prescribed drug dosage must be maintained throughout the trial period. Additionally, medications employed for the temporary treatment of conditions other than PD may be allowed after consultation with the investigator. All concomitant medications, irrespective of their purpose, should be documented with detailed drug information, including product name, dose, purpose and duration of administration, etc., in the case report forms (CRF). While there are no drugs that are pre-determined to be prohibited, the investigator retains the discretion to restrict the use of medications that may potentially influence the trial outcome, such as corticosteroids, female hormones, etc. This approach ensures thorough documentation and monitoring of medication usage throughout the study.

### Outcomes

The primary outcome of this study is the mean change in MDS-UPDRS Part III score from baseline to 8 weeks, which is a validated assessment tool is employed to evaluate the motor symptoms in PD patients [20]. MDS-UPDRS Part III scores can range from 0 to 132, with a higher score indicating worse clinical progression. Secondary outcome measures will include the MDS-UPDRS Part III score from baseline at 4 and 12 weeks, MDS-UPDRS (total) score from baseline at 4, 8, and 12 weeks, International Physical Activity Questionnaire (IPAQ) Short Form, Parkinson Self Questionnaire (PSQ, developed by researchers), Parkinson’s Disease Sleep Scale (PDSS), Timed Up and Go test (TUG) data, GAITRite Electronic Walkway Platinum metrics, Functional Near-Infrared Spectroscopy (fNIRS) measurements, smart band outcomes (number of steps per day), gut microbiome analysis results, and iris connective tissue texture and density. The details are shown in Table 2.

**Table 2 pone.0303156.t002:** Outcomes.

**Primary outcome measure**	**Time frame**
Movement Disorder Society Unified Parkinson’s Disease Rating Scale Part III (MDS-UPDRS Part III)	Change from baseline MDS-UPDRS Part III score at 8 weeks
**Secondary outcome measures**	**Time frame**
Movement Disorder Society Unified Parkinson’s Disease Rating Scale Part III (MDS-UPDRS Part III)	Change from baseline MDS-UPDRS Part III score at 4 and 12 weeks
International Physical Activity Questionnaire Short Form (IPAQ)	Change from baseline IPAQ score at 4, 8 and 12 weeks
Parkinson Self Questionnaire (PSQ), developed by researchers	Change from baseline Parkinson Self Questionnaire results at 4, 8 and 12 weeks
Parkinson’s Disease Sleep Scale (PDSS)	Change from baseline PDSS score at 4, 8 and 12 weeks
Timed up and go (TUG) test	Change from baseline TUG time in seconds at 8 and 12 weeks
GAITRite Electronic Walkway Platinum	Change from baseline GAITRite parameters at 8 and 12 weeks
Functional near-infrared spectroscopy (fNIRS)	Change from baseline fNIRS results at 8 and 12 weeks
Smart band outcomes (Number of steps per day)	Change from baseline daily steps at 4, 8 and 12 weeks
Movement Disorder Society Unified Parkinson’s Disease Rating Scale (MDS-UPDRS)	Change from baseline MDS-UPDRS score at 4, 8 and 12 weeks
Gut microbiome analysis results	Change from baseline at 8 weeks
Iris imaging 1 (Visible light image)	Iris connective tissue texture, baseline
Iris imaging 2 (Infrared image)	Iris connective tissue density, baseline

### Participant timeline

Among patients who applied to participate in this trial and signed the ICF, the following items will be checked for eligibility assessment: vital signs, the HY scale, the MMSE-K, demographic survey, medical and treatment history, laboratory tests, electrocardiogram, and chest X-ray. Upon random assignment to either the experimental or control group, participants will undergo treatment for a duration of 8 weeks in accordance with their respective group assignments. The MDS-UPDRS Part III, IPAQ, PSQ, PDSS, and economic evaluation questionnaire will be administered four times (0th, 4^th^, 8^th^, and 12^th^ week). TUG, GAITRite, and fNIRS measurements will be taken three times (0^th^, 8^th^, and 12th week). Gut microbiome specimens will be collected and analyzed twice: once at baseline and once at 8^th^ week. Before collecting human specimens, additional consent will be obtained for collection and use of biological specimens.

### Sample size

The hypothesis of this clinical trial is as follows:

H0 (null hypothesis): μ_t_ = μ_c_H1 (alternative hypothesis): μ_t_ ≠ μ_c_

μ_t_ denotes the average change in MDS-UDPRS Part III score from baseline to 8 weeks in the treatment group (MARS-PD treatment), and μ_c_ denotes the average change in MDS-UDPRS Part III score from baseline to 8 weeks in the control group (usual care). The experimental and control groups will be recruited in a one-to-one ratio.

For the determination of the sample size, we referenced a previous study that closely resembled our current investigation in terms of research design, treatment period, treatment method, number of participant visits, and outcome variables [21]. In the study conducted by Hackney and Earhart, a total of 33 patients diagnosed with PD were enrolled, with 17 participants in the exercise (Tai Chi) group and 16 in the control (no intervention) group. The treatment period lasted 10–13 weeks, with a total of 20 treatment sessions. One of their outcome variables was the UPDRS motor subscale (Part III). The observed average change in UPDRS Part III scores for the treatment and control groups were -1.5 ± 6.6 and 4.3 ± 5.6, respectively. The mean difference in effect between the Tai Chi group and control group was calculated as 5.8, with a pooled standard deviation was 6.1. These parameters from the previous study served as a basis for informing the sample size calculation in our current research design.

We used a conservative value of 5 for the mean difference of the effect and 6.5 for the standard deviation to calculate the number of test subjects to confirm the effect of the experimental group compared to the control group in this study. According to Shulman et al. [22] and Sánchez-Ferro et al., [23] the minimal clinically important difference (MCID) for UPDRS Part III is 2.3 and 5, respectively. In the meantime, Horváth et al. [24] estimated that the MCID for MDS-UPDRS Part III is between 2.3 and 2.7 points. Therefore, the proposed mean difference of the effect of 5 is equal to or greater than the MCID that was previously reported by the studies. Substituting this into the calculation formula [25] results in approximately 36 people per group as shown below. Considering the dropout rate of 20%, a total of 88 clinical trial subjects, 44 per group, are required. The criteria for dropout is specified in the protocol (S2 Appendix).

$$\frac{2*{\left(Z_{1-\frac{\alpha }{2}}+Z_{1-\beta }\right)}^{2}*\sigma^{2}}{\mu_{t}-\mu_{c}}=\frac{2{\left(1.96+1.28\right)}^{2}*6.5^{2}}{5^{2}}\sim 36$$

Where α (two-tailed test significance level) = 0.05; β (type 2 error) = 0.1; 1-β (power) = 90%.

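### The stated 36 evaluable, 20% dropout, 44 per group and 90% power do not quite agree, and the SD of 6.5 looks optimistic against the team's own pilot

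*Protocol article*

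**What the plan says.** The Sample size section of the protocol article sets the planning values: "We used a conservative value of 5 for the mean difference of the effect and 6.5 for the standard deviation". They come from a 33-patient Tai Chi study using the older UPDRS motor subscale, whose changes in the "treatment and control groups were -1.5 ± 6.6 and 4.3 ± 5.6, respectively". The article gives that study's difference as "calculated as 5.8, with a pooled standard deviation was 6.1".

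The error rates are "α (two-tailed test significance level) = 0.05; β (type 2 error) = 0.1; 1-β (power) = 90"%. The formula uses normal quantiles, and the section says that it "results in approximately 36 people per group as shown below". Enrolment follows: "Considering the dropout rate of 20%, a total of 88 clinical trial subjects, 44 per group, are required". The step from 36 to 44 is not shown.

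The Efficacy evaluation section names an independent t-test on the change at 8 weeks as the primary test. Analysis of covariance replaces it only if the groups differ significantly at baseline.

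The Objectives section reports the team's uncontrolled pilot of the same intervention (16 sessions over 8 weeks) on MDS-UPDRS Part III: "from 20.00 ± 11.78 to 8.85 ± 5.54, p = 0.003". The Sample size section does not mention these data.

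**The concern.** There are two separate issues.

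First, the evaluable number, the dropout allowance, the enrolled number and the power are given as one consistent set, and they are not. The formula is also a normal approximation, while the planned test is a t-test.

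Second, the SD drives the calculation, because the required number grows with its square. The article holds variability data from the intervention, scale and duration under test, yet it plans from another intervention on an older version of the scale. If the variability of change is nearer to what the pilot suggests, the real power for 5 points is below the stated figure. A non-significant result would then be read as firmer evidence against a 5-point effect than it is.

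**Working it through.** **Inputs.** From Sample size: difference 5, SD 6.5, two-sided alpha 0.05, power 90%, 36 evaluable and 44 enrolled per group, dropout 20%. From Objectives: pilot SDs 11.78 (before) and 5.54 (after). The pre-post correlation r is not given and is an assumption throughout.

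**1. The plan's own figure.** n = 2(1.96 + 1.28)² × 6.5² / 5² = 2 × 10.4976 × 42.25 / 25 = 35.48, so 36 per group. This reproduces. (The symbolic denominator is printed unsquared, but the numerical step uses 5², so nothing changes.)

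**2. Dropout.**
- 36 / (1 − 0.20) = 45 per group, 90 in total.
- 44 × 0.80 = 35.2, so 35 whole patients per group.
- 44 keeps 36 only if dropout is at most 8/44 = 18.2%.
- From the unrounded figure, 35.48 / 0.80 = 44.35. This is 44 to the nearest integer, or 45 if rounded up.

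**3. Power of the t-test** (noncentral t, difference 5, SD 6.5):

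| Evaluable per group | Power |
|---|---|
| 35 | 88.7% |
| 36 | 89.6% |
| 37 | 90.4% |

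So 37 evaluable per group are needed for 90%, and the design as stated gives 88.7%, which is 1.3 points short.

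**4. The SD against the cited study.** √[(16 × 6.6² + 15 × 5.6²)/31] = 6.1, as stated. Planning with 6.5 instead of 6.1, and with 5 instead of 5.8, raises the sample size in both cases.

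**5. The SD against the pilot.** SD of change = √(11.78² + 5.54² − 2r × 11.78 × 5.54) = √(169.46 − 130.52r).
- At r = 1 it is 6.24, the lowest possible value.
- It equals 6.5 when r = (169.46 − 42.25)/130.52 = 0.975.

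**6. Power at 35 per group for 5 points, by assumed r.** The middle column gives the treated arm the pilot SD and the control arm 6.5, using √[(SD² + 6.5²)/2]. The last column gives both arms the pilot SD.

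| Assumed r | Pilot change SD | Power, treated arm only | Power, both arms |
|---|---|---|---|
| 0.9 | 7.2 | 85% | 82% |
| 0.8 | 8.1 | 80% | 72% |
| 0.7 | 8.8 | 76% | 65% |
| 0.5 | 10.2 | 67% | 52% |

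**7. Baseline-adjusted ANCOVA.** With equal variances at baseline and week 8, change SD 6.5 and an assumed r of 0.7, the residual SD is 6.5 × √[(1 + 0.7)/2] = 5.99. Power at 35 per group is about 93%.

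**The case against.** The arithmetic gap is close to rounding. Dividing the unrounded 35.48 by 0.8 gives 44 to the nearest whole number, the normal formula is a common convention, and 1.3 points of power would change no decision about running the trial. This stands, and it is why 88 can be kept. The statement can still be corrected, because a reader who takes 36 and 20% at face value cannot arrive at 44.

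Thirty-five is a count of completers. Under Statistical analysis the full analysis set is primary, imputation is foreseen, and not every dropout is excluded. More than 35 per group may therefore contribute, so the 88.7% holds only if the 20% provide no week-8 data.

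Some stronger readings are tempting, and the article does not support them:
- A reader might infer that 44 came from multiplying 36 by 1.2. No inflation step is printed, so the route is unknown.
- A reader might infer that the pilot contradicts 6.5. It gives SDs at two time points but no SD of change, sample size or named test, and 6.5 is attainable, though only at a near-perfect correlation.
- A reader might call the word conservative wrong. Against the cited study's 5.8 and 6.1 it is accurate.
- A reader might take the both-arms column as the expected power. The pilot had no control arm and says nothing about control variability. The only control-arm change SD in the article is 5.6. With that value in the control arm, power at 35 per group would be about 84% at r = 0.8 and 71% at r = 0.5.

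The pilot's mean change, 20.00 − 8.85 = 11.15, also far exceeds 5. But it is uncontrolled, and 5 is the difference for which 90% power is claimed.

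**Conclusion.** The point holds in a limited form. On the article's own inputs the four stated figures do not fit together, and power after the planned dropout is 88.7% instead of 90%. This is a small error, conditional on dropouts giving no week-8 data.

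The SD is the more consequential part, but it is less certain. Unless the pilot's pre-post correlation was about 0.975 or higher, its change SD exceeded 6.5, and the article does not discuss this. Over assumed correlations of 0.9 to 0.5, power would be about 85% to 67% if only the treated arm varies that much, and 82% to 52% if both arms do. These ranges show sensitivity and are not estimates. They do not establish that the trial is underpowered.

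**What to change.** Keep 88 and restate the power along these lines: 88 randomised leaves about 35 per group after 20% dropout, giving 88.7% power for a 5-point difference at SD 6.5 (two-sided t-test).

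Report the pilot's SD of change, justify 6.5 against it, and give power over a range of SDs labelled as assumptions, with the treated-arm-only and both-arms cases shown separately. If conservative is kept, say that it is relative to the Tai Chi study. This part costs wording and one pilot summary figure, and needs no extra patients.

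Make baseline-adjusted ANCOVA the primary analysis unconditionally, replacing the rule that uses it only after a significant baseline difference. The baseline score is already collected. The 93% in step 7 rests on SD 6.5, equal variances and r = 0.7. The pilot's unequal SDs do not meet the equal-variance assumption, so that figure should carry its conditions. This part is more than wording: it changes the primary analysis and, under Study protocol modifications, must be reported to and approved by the ethics board, with participants informed.
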